## Abstract

**Introduction:** The crowding of emergency departments (ED) has been a growing problem for years, putting the care of critically ill patients increasingly at risk. The INDEED project's overall aim is to get a better understanding of ED utilization and to evaluate corresponding primary health care use patterns before and after an ED visit while driving forward processes and methods of cross-sectoral data merging. We aim to identify adequate utilization of EDs and potentially avoidable patient contacts as well as subgroups and clusters of patients with similar care profiles.

**Methods:** INDEED is a joint endeavor bringing together research institutions and hospitals with EDs in Germany. It is headed by the Charité–Universitätsmedizin Berlin, collaborating with Otto von Guericke University Magdeburg, Technische Universität Berlin, the Central Research Institute of Ambulatory/Outpatient Health Care in Germany (Zi), and the AOK Research Institute as part of the Federal Association of AOK, as well as experts in the technological, legal, and regulatory aspects of medical research (TMF). The Institute for Information Technology (OFFIS) was involved as the trusted third party of the project. INDEED is a retrospective study of approximately 400,000 adult patients with statutory health insurance who visited the ED of one of 16 participating hospitals in 2016. The routine hospital data contain information about treatment in the ED and, if applicable, about the subsequent hospital stay. After merging the patients' hospital data from 2016 with their outpatient billing data from 2 years before to 1 year after the ED visit (years 2014–2017), a harmonized dataset will be generated for data analyses. Due to the complex data protection challenges involved, first results will be available in 2021.

**Discussion:** INDEED will provide knowledge on extracting and harmonizing large scale data from varying routine ED and hospital information systems in Germany. Merging these data with the corresponding outpatient care data of patients offers the opportunity to characterize the patient's treatment in outpatient care before and after ED use. With this knowledge, appropriate interventions may be developed to ensure adequate patient care and to avoid adverse events such as ED crowding.

## Introduction

Emergency departments (EDs) in many countries face the challenge of crowding and increasing numbers of ED visits (1). The number of ED visits has increased over the last decades in almost all OECD countries (2). Annually around 21 million patients are treated in German EDs (3). From 2009 to 2015 the number of patients in EDs increased by 42% for outpatient care while inpatient emergency cases grew by 20% (4). One reason for the rising ED patient numbers in outpatient treatment is the utilization of the EDs' 24/7 available medical expertise for minor health problems. This is due to several reasons, with patients often citing health anxiety and lack of alternatives (5–7). More than 50% of ED patients do not require subsequent hospital inpatient treatment, but approximately only 20% could have been treated in the outpatient sector/outpatient care (8, 9). Care provision for patients with low urgency health needs in the emergency setting is currently being heavily debated as hospital-based outpatient care is associated with high costs and does not offer the same continuity as primary care in the outpatient sector (10). Additionally, a large share of acute care patients receiving inpatient treatment after an ED visit are diagnosed with Ambulatory Care Sensitive Conditions (ACSC), i.e., frequent chronic and acute diagnoses for which inpatient care could have been avoided by timely and adequate measures in the outpatient care sector (11–14).

Therefore, the INDEED-project (Utilization and cross-sectoral patterns of care for patients admitted to emergency departments in Germany) will (1) explore the utilization and cross-sectoral patterns of care for patients admitted to EDs in Germany, and (2) provide a framework for future data linkage that takes into account the ethical, legal, and technological aspects for creating a unique data set by merging data from different sectors over a time period of 3 years.

## Methods

### Design

INDEED is designed as a retrospective evaluation of three different scenarios based on different data sources (Figure 1), with the aim of illustrating ED use in 2016. The main research question focuses on scenario 1, comprising selected routinely collected data on emergency treatment and possible subsequent hospital stay from 16 EDs (data source 1: hospital data), merged with the data of these patients from their routine outpatient health care for the period from 2 years before to 1 year after their ED stay (data source 2: outpatient care data) (15, 16).

**Figure 1 F1:**
[figure not shown]
Project scenarios 1–3 using the evaluation of different data sources.

Scenario 2 utilizes the data for all patients in Germany with statutory health insurance and an outpatient ED visit in 2016 from the collection of nationwide outpatient billing data of the Associations of Statutory Health Insurance Physicians (KV: Kassenärztliche Vereinigungen). Since outpatient treatment of all statutory health insurance companies are invoiced via the KV, including outpatient ED treatment (17), scenario 2 will allow the nation-wide representativeness of scenario 1 to be assessed.

Similarly to scenario 2, as another independent and parallel analysis, scenario 3 will analyze the outpatient and inpatient care before and after an emergency treatment in 2016 using routine data from a system of eleven regional health care funds of AOK (Allgemeine Ortskrankenkassen, statutory health insurance companies), that insure more than 26 million people in Germany (data source 3: AOK routine data).

The present publication focuses on scenario 1.

In order to achieve the goals of INDEED scenario 1, inclusion of all eligible patients is crucial to guarantee representativeness of the study population. Treatment in an ED is generally carried out in an exceptional situation; in some cases patients are not able to give consent due to urgency of treatment and the short treatment period. Therefore, individual declarations of consent are/were not intended in the context of this retrospective secondary use of routine data for INDEED. Instead, data processing had to be based on a statutory norm of consent, requiring complex technical and organizational measures as described below.

### Study Population

EDs were recruited by approaching clinics from an existing ED-network, AKTIN (18), as well as at scientific events of the Emergency Medicine societies in Germany. We intended to recruit hospitals of different sizes throughout Germany. The main requirement for participation was the availability of electronic documentation in the ED in 2016. Data protection regulations in the respective federal states were also taken into consideration and three categories of feasibility were assigned to the federal states of Germany (green, yellow, red). It was examined whether there was a legal norm of permission at the state level to conduct the project without prior informed consent of patients (green−7 times assigned) and which requirements, if any, were associated with this (yellow−3 times). In the absence of such or significant restrictions, the project was assigned to the red category (6 times). Regardless of the categorization, it should be noted that in each case a considerable great effort of argumentation was done to obtain the necessary approvals.

Patients in the participating EDs were included if they had at least one ED visit in 2016 and were insured in one of the existing German statutory health insurance companies, which cover about 87% of the population in Germany (19). We exclude patients with private health insurance as well as cases that are billed via the German Social Accident Insurance. The latter covers accidents at work or recognized occupational diseases. Although they constitute a relevant proportion of cases in German EDs, they are covered by a different regulatory framework. Minimum age has to be 20 years on January 1st 2016, as this corresponds to a minimum age of 18 years at the beginning of our observation period (January 1st, 2014) in the outpatient care data.

The final study population for scenario 1 are ED patients originating from 16 participating EDs in Germany (Figure 2). In addition, basic data of ED and hospital structures are collected according to standards used in previous projects such as the German DGINA (German society for interdisciplinary emergency and acute medicine) network (20), to allow a basic description of the participating EDs and hospitals.

**Figure 2 F2:**
[figure not shown]
Overview of the 16 participating hospitals with emergency departments (red dots) and the German federal states (in gray) where the regional Associations of Statutory Health Insurance Physicians provided outpatient health care data. “Charité Berlin (1–3)” designated 1 = Campus Virchow Klinikum, 2 = Campus Mitte, 3 = Campus Benjamin Franklin.

### Data Sources, Data Flow, and Management

In scenario 1, data from two different sources will be merged. Firstly, ED and inpatient data from 2016 will be extracted from 16 hospitals with EDs across Germany. This will include general information about the patient, ED treatment data, vital signs, blood parameters, and data from a subsequent inpatient stay. Secondly, for the time period from 2014 to 2017 outpatient care data will be extracted for all patients who were treated at least once in 2016 in one of the participating EDs. This data will be provided by the Zi after collection from the regional Associations of Statutory Health Insurance Physicians (KV) of the federal states corresponding to the location of the participating EDs. These data sets will include general information about the patient, information on the medical practice and practitioner, diagnoses, performed procedures and their costs, and information about the medication and their costs.

Clinical data usually lack sufficient standardization due to different software systems used for documentation in the EDs, different treatment pathways, different routines and situations, with an additional lack of time for sufficient documentation in emergency situations. The degree of heterogeneity and need for further homogenization and data-coarsening will be determined after data extraction from all hospitals has been completed. Data processing will take place at the INDEED Central Data Management (CDM) office. The list of variables to be extracted from the hospitals and the respective outpatient care data are presented in Supplementary Table 1.

The data handling procedures from the local hospital queries, the linkage of both data sources (hospital and outpatient care data), up to the final dataset are quite complex: challenges include (i) extracting data from different documentation systems, (ii) cleaning and harmonizing them, and (iii) linking these two data sources (hospital data and outpatient care data) at the patient level, all while conforming to the different and complex data protection rules (Figure 3). All processes regarding data linkage follow and adhere to the “Good Practice Data Linkage” (21).

**Figure 3 F3:**
[figure not shown]
Schematic overview of the data flow in INDEED scenario 1. ED, emergency department; OFFIS, Institute for Information Technology; Oldenburg, trusted third party of the project data; CDM, Central Data Management; KV-data, the outpatient care data originating from the KV; DSSG, Service & Support GmbH (KV data trusted third party); AV-data, medical prescription data; C-Not, Emergency and Acute Medicine (CVK, CCM); Charité, Universitätsmedizin Berlin; C-Soz, Institute of Medical Sociology and Rehabilitation Science; Charité, Universitätsmedizin Berlin; C-Epi-DA, Institute for Social Medicine, Epidemiology and Health Economics; Charité, Universitätsmedizin Berlin, Data analizes; UK Magdeburg, Department of Trauma Surgery; Otto von Guericke University Magdeburg, MiG Berlin, Dept. Health Care Management, Berlin University of Technology; Zi, Central Research Institute of Ambulatory/Outpatient Health Care in Germany.

The data flow (step 1 to 9) is described in more detail in the following section. All data containers are signed and RSA-4096-encrypted (special encryption method named after Rivest, Shamir and Adleman) and all data transfers are handled via SSH/TSL, secured by encryption on transfer level and receiver oriented encryption on file level (22).

#### Extraction and Pseudonymization of Hospital Data

For the linkage of the two data sources (hospital and outpatient care data), an identification number is needed that is unique for each patient and available in both data sources (Figure 3, Step 1). This linking will be based primarily on the electronic health insurance card number (eGK-Nr) and, secondarily, on a combination of surname, first name, and date of birth (Name-DOB; DOB: date of birth) if the eGK-Nr is missing or erroneous. However, in the end it only worked for the first strategy based on the eGK-Nr, due to software issues and lack of time to fix this problem. Of the final 353.926 ED-patients, 290.883 (82.2%) had a valid eGK number, could be identified in the KV data and successfully linked. The eGK-Nr, Name-DOB and the internal hospital case numbers (Case-Nr) for each ED patient visit compose the patients' Identifying Data (IDAT). A computer software, which was specifically developed for the INDEED-project by OFFIS, pseudonymizes these IDAT after final data extraction using a cryptographic hash function. The data set containing the IDAT, the Medical information user Data (MDAT) and an added line identifier (L-ID) is split into separate IDAT and MDAT datasets, with the L-ID in both, and consequently into different encrypted containers. The MDAT include all the information regarding treatment during the ED visit and the possible subsequent inpatient stay. The MDAT can only be decrypted in CDM. Since hospital data will be obtained from different documentation systems within each hospital the above process must be performed on numerous data sets for each hospital. Although these numerous data sets could potentially be merged on-site with the Case-Nr it will be performed in CDM at a later stage, to ensure the highest data quality.

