#### Preparation of Data Linkage at OFFIS: Hospital Data

OFFIS will create a list of INDEED patients based on the pseudonymized eGK-Nr and Name-DOB in the IDAT, additionally using the Case-Nr if inconsistencies occur (Figure 3, Step 3).

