### Sample Size Estimation and Statistical Analyses

We assumed that 15 to 20 EDs across Germany will result in a sample of EDs yielding different hospital structures and locations. We were assuming that these EDs have an average of about 34,000 cases per year. This assumption is based on a general estimate of the average number of cases in German EDs (3, 23, 24), and yields an expected total number of 510,000 to 680,000 cases. However, since about 15% of patients have multiple emergency contacts per year (based on ED data from Charité in Berlin), the estimated total number of patients is around 442,000 to 589,000. Applying the study's inclusion criteria (e.g., adult patients with statutory health insurance) will limit the number of eligible patients to about 86.5% of the total population in Germany in 2016 (24). Thus, we expect a total of approximately 400,000 ED patients to be available for our data analysis.

With this sample size, precise estimates of prevalences are possible even within small subgroups: for example, in any given subgroup of 1% of the total number of patients (i.e., approximately 4,000 patients) a prevalence of 50% could be estimated with a precision of ±1.6% (half width of a two-sided exact 95% confidence interval). In this example, a prevalence of 50% was chosen, as this proportion shows the greatest variation. A prevalence higher or lower than 50%, or subgroups larger than 1%, would lead to narrower confidence intervals, i.e., more accurate estimates.

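### 17.8% of ED patients have no linked outpatient data, and the article neither lists this as a limitation nor reflects it in its precision figure

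*Protocol article*

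**What the plan says.** The Design section defines scenario 1, which carries the main research question, as hospital data from 16 EDs merged with the same patients' outpatient data. In explaining why no individual consent is sought, it says that "inclusion of all eligible patients is crucial to guarantee representativeness of the study population".

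Under Extraction and Pseudonymization of Hospital Data, linkage is to rest first on the eGK-Nr. The fallback is to link "secondarily, on a combination of surname, first name, and date of birth (Name-DOB; DOB: date of birth) if the eGK-Nr is missing or erroneous". The same paragraph then reports that the fallback failed: "in the end it only worked for the first strategy based on the eGK-Nr, due to software issues and lack of time". It goes on to give the yield: "Of the final 353.926 ED-patients, 290.883 (82.2%) had a valid eGK number, could be identified in the KV data and successfully linked".

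Two later steps are written as if both keys operated. Preparation of Data Linkage at OFFIS says that "OFFIS will create a list of INDEED patients based on the pseudonymized eGK-Nr and Name-DOB in the IDAT", and Data Linkage (OFFIS) and Data Transfer to Central Data Management again names both keys.

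Under Sample Size Estimation and Statistical Analyses, precision is given for the case that "in any given subgroup of 1% of the total number of patients (i.e., approximately 4,000 patients") are analysed: "a prevalence of 50% could be estimated with a precision of ±1.6% (half width of a two-sided exact 95% confidence interval").

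The limitations, under Expected Results and Status Quo, cover the non-random choice of hospitals, privately billed services and accident-insurance cases. Patients who could not be linked are not mentioned.

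**The concern.** More than one patient in six is missing from the linked data that define scenario 1, after a planned safeguard failed. The questions on outpatient care before and after the ED visit can be answered only for linked patients, and the central question on adequate, inadequate or avoidable use is posed within the linked scenario. If linkage is related to what is being estimated, prevalences and cluster sizes from linked patients will not describe the ED population.

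The article gives some reason not to presume a random loss. It describes different software systems and little time to document in emergencies (Data Sources, Data Flow, and Management), and data availability and quality that varied between EDs (Expected Results and Status Quo). These remarks concern ED data in general, so they make selective linkage plausible without showing it.

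The planned representativeness check does not settle the matter. It compares scenario 1 with scenarios 2 and 3. Scenario 2 holds outpatient ED visits only, so it cannot reveal under-linkage of admitted patients, and scenario 3 covers one group of insurers. The article also concedes that the hospitals are not representative of Germany. Any discrepancy found would therefore mix selection of hospitals with selection by linkage.

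**Working it through.** **Inputs.** From Extraction and Pseudonymization of Hospital Data: 353,926 final ED patients, 290,883 linked. From Sample Size Estimation: a 1% subgroup of about 400,000, i.e. 4,000, at 50% prevalence, with a two-sided exact 95% interval. Not in the article, and therefore assumed over a range: d, the prevalence in linked minus the prevalence in unlinked patients.

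**1. The article's own figures.**
- Linkage rate: 290,883 / 353,926 = 0.8219, matching the stated 82.2%.
- Precision: the Clopper-Pearson interval for 2,000 of 4,000 has a half-width of 1.56 points, which rounds to the stated 1.6.

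Both reproduce.

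**2. Unlinked patients.** 353,926 − 290,883 = 63,043; u = 63,043 / 353,926 = 0.178.

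**3. Precision on the cohorts obtained** (same exact method, 50% prevalence):
- 1% of all 353,926 patients: n = 3,539, half-width 1.66 points.
- 1% of the 290,883 linked patients: n = 2,909, half-width 1.83 points.
- All 290,883 linked patients: half-width 0.18 points.

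**4. Selection error of a linked-only prevalence.** The prevalence in all patients is (1 − u) × p(linked) + u × p(unlinked). Subtracting this from p(linked) gives

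error = u × [p(linked) − p(unlinked)] = 0.178 × d.

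| Assumed d (points) | Error (points) |
|---|---|
| 1 | 0.18 |
| 5 | 0.89 |
| 9 | 1.60 |
| 10 | 1.78 |
| 20 | 3.56 |
| 30 | 5.34 |

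The error reaches 1.6 points at d = 1.6 / 0.178, about 9 points. For a whole-cohort prevalence, a d of about 1 point already gives an error as large as the random half-width of 0.18.

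**5. Worst-case bounds at a linked prevalence of 50%.** If no unlinked patient has the characteristic: 0.8219 × 0.5 = 41.1%. If all have it: 41.1% + 17.8% = 58.9%. The error cannot exceed 8.9 points in either direction.

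**Caveat.** u = 0.178 is the share in the whole cohort. The unlinked share within any subgroup is not given, so the comparison with the subgroup figure of 1.6 is indicative only.

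**The case against.** Four stronger readings are tempting, and the article supports none of them.

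- *The linked analysis carries an error far larger than ±1.6 points.* This needs d well above 9 points, and no difference between linked and unlinked patients is reported. At a d of 5 the error is 0.89 points.
- *The failed fallback caused the whole 17.8%.* The 82.2% requires a valid number, presence in the outpatient data and a successful link. Those data come only from the regions where the EDs lie, so some patients may not be in them at all, and matching on name and date of birth could not recover these.
- *The plan commits to an unweighted analysis of linked patients.* The article does not say so. It is a condensed account, any analysis plan is not shown, and silence on weighting is not an error.
- *Card numbers go unread in the most urgent cases.* The article says nothing of the kind.

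Other points on that side also have force. The non-linkage is openly disclosed. The sentence on including all eligible patients argues for working without consent and does not claim complete linkage. National representativeness is disclaimed. The two later steps may describe only how pseudonym lists are built, since name and date of birth belong to the identifying data whether or not matching on them worked.

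What remains is that the disclosure stays in a data-flow paragraph. The loss reaches neither the limitations nor the precision statement, and no described check isolates its effect.

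**Conclusion.** The point holds in conditional form. That 63,043 patients (17.8%) are unlinked is a fact of the article; that this biases the results is a possibility whose size depends on an unreported d. A linked-only prevalence would be off by 0.178 × d, which passes the quoted 1.6 points only if d is above about 9, and the worst case at 50% is a range of 41.1% to 58.9%. The precision figure is correct for its planning assumption. It covers sampling error alone and is somewhat optimistic for the linked cohort obtained (about ±1.83 points for a 1% subgroup).

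This is an inexpensive improvement worth making, not proof that the linked results are wrong. It assumes that the reported counts are final and that the population of interest is all 353,926 included ED patients.

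**What to change.** 1. Keep the 353,926 as the target population and report non-linkage by cause: missing or invalid eGK-Nr, not found in the regional outpatient data, other.
2. Compare linked with unlinked patients on the hospital variables available across EDs.
3. For the headline prevalences, show an inverse-probability-of-linkage weighted estimate beside the unweighted one, together with worst-case bounds. The linkage model can include the centre number: Transfer of Hospital Data allows centre adjustment but bars comparative centre analyses, so linkage should not be reported centre by centre.
4. Answer questions that need hospital data only on all 353,926 patients.
5. Restate precision on the linked number and say that it covers sampling error only.
6. Add non-linkage to the limitations, and qualify the Design sentence on including all eligible patients.
7. Reconcile the two OFFIS linkage steps with the report that only the eGK-Nr route worked.

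**Cost.** The hospital data are already in Central Data Management, so this needs one comparison table, one linkage model, some further analysis work and wording. Intervals widen slightly under weighting. Weighting can correct only for recorded variables, and these were recorded unevenly between EDs, which is why the bounds should accompany it.
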